## Abstract

**Background:**

Hypertension, the leading cause of morbidity and mortality, affects more than 1 billion people and is responsible globally for 10 million deaths annually. Hypertension can be controlled on a national level; in Canada, for example, awareness, treatment, and control improved dramatically from only 16% in 1990 to 66% currently. The ongoing development, dissemination, and implementation of Hypertension Canada’s clinical practice guidelines is considered to be responsible, in part, for achieving these high levels of control and the associated improvements in cardiovascular outcomes. A gap still exists between the evidence and the implementation of hypertension guidelines in Indigenous communities in Canada, as well as in low- and middle-income countries (LMICs). The rapid rise in the ownership and use of mobile phones globally and the potential for texting (short message service, SMS) to improve health literacy and to link the health team together with the patient served as a rationale for the Dream-Global study in both Canada and Tanzania.

**Objective:**

The primary objective of the Dream-Global study is to assess the effect of innovative technologies and changes in health services delivery on blood pressure (BP) control of Indigenous people in Canada and rural Tanzanians with hypertension using SMS messages and community BP measurement through task shifting with transfer of the measures electronically to the patient and the health care team members.

**Methods:**

This prospective, randomized blinded allocation study enrolls both adults with uncontrolled hypertension (medicated or unmedicated) and those without hypertension but at high risk of developing this condition who participate in a BP screening study. Participants will be followed for at least 12 months.

**Results:**

The primary efficacy endpoint in this study will be assessed by analysis of variance. Descriptive data will be given with the mean and standard deviation for continuous data and proportions for ordinal data. Exploratory subgroup analyses will include analysis by community, sex, mobile phone ownership at baseline, and age. The knowledge gained from the text messages will be assessed using a questionnaire at study completion, and results will be compared between the groups.

**Conclusions:**

This study is expected to provide insights into the implementation of an innovative system of guidelines- and community-based treatment and follow-up for hypertension in Indigenous communities in Canada and in Tanzania, an example of an LMIC. These insights are expected to provide the information needed to plan scalable and sustainable interventions to control BP virtually anywhere in the world.

**Trial Registration:**

Clinicaltrials.gov NCT02111226; https://clinicaltrials.gov/ct2/show/NCT02111226 (Archived by WebCite at http://www.webcitation.org/6v7IdYzZh)

## Introduction

### Background and Rationale

Worldwide, hypertension is the leading cause of morbidity and mortality, affecting more than 1 billion people and responsible for 10 million deaths annually [1]. Hypertension increases the burden of disease globally through cardiovascular disease, kidney disease, and dementia [2-4]. For every 20-mm Hg increase in systolic blood pressure (BP) above 115 mm Hg, and every 10-mm Hg increase in diastolic BP above 75 mm Hg, there is a doubling in the risk of mortality from cardiovascular disease [5]. Placebo-controlled studies of BP lowering in people with hypertension demonstrate a 17% reduction in major cardiovascular events for every 5-mm Hg fall in systolic BP [6]. Hypertension can be controlled at the national level. For example, BP control improved dramatically in Canada from only 16% in 1990 to 66% at present [7,8]. The ongoing development, dissemination, and implementation of Hypertension Canada’s clinical practice guidelines is considered to be responsible to a great extent for achieving these high levels of awareness, treatment, and control, which in turn are linked to improved cardiovascular outcomes [9]. However, although BP control and treatment have improved nationally, the improvements are not distributed equally at the regional level linked to disparities in the determinants of health.

In Tanzania and other low-income countries, hypertension control presents a significant challenge because of deficiencies in primary health care resources such as health care providers and antihypertensive medications. Tanzania, like many countries in sub-Saharan Africa, is experiencing an epidemiological transition from a disease burden of mostly communicable diseases and injuries to a disease burden increasingly dominated by noncommunicable diseases such as cardiovascular disease, diabetes, and cancer [10]. The approaching wave of chronic diseases that require monitoring and access to drugs is a threat to the health care system in Tanzania. At present, in Tanzania, the prevalence of hypertension is between 35% and 40% in adults, with awareness of hypertension only 20%, treatment 10%, and control approximately 5% [11]. Many of the determinants of health affecting Canada’s Indigenous communities are shared by people in low- and middle-income countries (LMICs) [12]. Thus, interventions that work in LMICs may have a role in Indigenous communities and other similar populations.

In Canada, rates of hypertension in Indigenous populations are 20%, similar to the rest of the country [13]. Although data for treatment and control rates in Indigenous populations are lacking, higher cardiovascular disease rates suggest poorer control. A framework for discussion on how to improve the prevention, management, and control of hypertension from 2011 to 2020 describes this situation and calls for Indigenous populations to have similar rates of BP surveys and health indicators as the rest of the population [14]. Inequities in the social determinants of health—poverty, in particular—lead to poorer health outcomes in Indigenous communities than in the general Canadian population [15]. The social determinants particularly important for Indigenous health include income, education, employment, living conditions, adequate housing, and access to culturally competent health services. Indigenous health is also affected by the consequences of colonialism, including loss of language and ways of life and dispossession of traditional lands. This has led to food insecurity; environmental deprivation; and spiritual, emotional, and mental disconnectedness [16,17]. Compounding these issues are frequent experiences of social exclusion, discrimination, and racism [18,19]. All of these issues must be considered when undertaking a research project with Indigenous communities.

The DREAM3 (Diabetes Risk Evaluation and Management) study demonstrated that clinical practice guidelines could be implemented in Canada’s First Nation’s Communities leading to improved BP control. This community-based participatory randomized controlled research study in a Northern Canadian First Nations community was conducted in response to the community’s goal of controlling BP in people with diabetes to prevent the progression of kidney disease [20]. The hypothesis tested was whether the implementation of a chronic care model implemented by the addition of a home and community care nurse to support the chronic care model could provide a more effective means of lowering BP than usual care. Our research showed that the implementation of the new model led to significantly better BP control [20]. Two years after the completion of the DREAM3 study, BP in the treatment arm remained controlled, and BP in the control arm had fallen equal to that of the treatment arm [21].

The DREAM3 program included many of the components of a sustainable chronic disease intervention initiative, which are as follows: (1) patient self-management and participatory care; (2) decision support tools and easy-to-use, evidence-based aids for providers; (3) clarity of delivery team roles with planned coordination; (4) clinical information system that can track the progress of chronic disease management; (5) organization of health care delivery to accommodate the needs of chronic disease management; and (6) involvement of community-wide partnerships [22]. Furthermore, there was a focus on refreshing health education of skilled staff and educating new health care providers about new processes. The insights from the DREAM3 program have been integrated in the Dream-Global study, with an emphasis on changes in health services delivery supported by technology. Dream-Global incorporates patient self-management and participatory care by using texting (short message service, SMS) with BP readings, which provide the patient with the information they need to understand and participate in their own management. In the Dream-Global study, rather than increasing the burden of the home and community care nurses, task shifting was used to optimize the efficiency of the health care team and a dashboard was developed to track progress for each community. The SMS messages helped to link members of the interprofessional team, including the participant, the community health resource (CHR), the home and community nurse, and the participant’s primary health care provider.

SMS text messaging has become more widespread in research since the Dream-Global protocol was developed. A recent meta-analysis has demonstrated that text messages increased adherence to drug therapy [23]. Most studies compare the use of SMS messages to usual care; the Dream-Global study is unique in comparing disease-specific active messages to passive messages alone and their impact on BP control.

The research program described in the Dream-Global protocol focuses on high BP prevention and control in First Nations communities in Canada and rural communities in Tanzania. It builds on our research as well as previous research on the efficacy and effectiveness of approaches to prevention and control of high BP. The program is designed to work within existing health systems and workflows [24]. The research program involves the active engagement of the participating communities. It is designed to be adaptive to the settings where the research is occurring; factors to be taken into consideration include social, economic, and cultural contexts; disparities in population health and disease burdens; existing health care models for chronic disease management; level of awareness of the importance of hypertension as a disease burden; and existence of national clinical practice guidelines designed to reduce the burden of hypertension. In Canada, Indigenous populations include First Nations, Métis, and Inuit people. The study recruited participants from six First Nations communities, all of whom lived on reserve. In Tanzania, this program is being implemented in rural communities in Hai district of the Kilimanjaro region. Due to differences in the structure and financing of the health care system in both countries, the protocols for each country vary in their design and implementation. The SMS intervention remains the same but in different languages (English in Canada and Swahili in Tanzania) [25].

The implementation of a complex intervention such as the Dream-Global program is strongly affected by cross-cultural relationships between local partners and outside researchers. Trickett and colleagues have argued that “culture pervades all aspects of community interventions” [26]. Strong community engagement and community-based participatory research (CBPR) are the necessary foundation for successful implementation of a pragmatic trial, particularly in diverse geographic and cultural contexts [24]. The CBPR approach developed for Dream-Global is designed to incorporate local knowledge in the research process by meaningfully engaging those affected by the issue under study in all aspects of the research. This research program is also informed by the Behavioral Change Wheel (BCW), an evidence-based theoretical model that explains the individual and system changes necessary to support hypertension management in low-resource settings [27]. The BCW model incorporates essential internal and external conditions necessary for behavioral change, including changes in supporting policies, mechanisms, and systems, and patients’ capability, opportunity, and motivation [27]. The long-term goals of the Dream-Global research program are listed in Textbox 1. The program is designed to engage local decision makers and community leaders to involve multiple stakeholders from a variety of sectors, including the food industry, nursing, medical health, and public health, and to function smoothly with existing community programs. The components of the intervention will be robustly evaluated both individually and together to understand the relative contribution of each component and the synergies between them.

### Objectives

In this paper, we outline the methods, tools, and processes of the Dream-Global research program. This research program was designed to integrate innovations in communications technology and health services delivery with the local realities of health care while taking into account each community’s unique circumstances regarding geography, the social determinants of health, and the interplay between local, provincial, and federal health care systems.

This study includes the development of a community readiness to participate in research tool, a project to understand the sources of dietary sodium and how to reduce it in a remote community, the development of mobile health technology to incorporate BP measurement by nonmedical health workers, the transmission of the measurement to health care providers and patients, the development of guidelines-based culturally appropriate SMS messages for BP management, and the testing of these messages for BP lowering in a multicommunity randomized controlled trial in both Canada and Tanzania. The background information is provided here for both parts of the study, but for pragmatic reasons, the Tanzanian portion of the study was delayed and a fuller protocol is being prepared for separate publication.

Dream-Global objectives.To ultimately reduce the prevalence of cardiovascular disease, including heart attack and stroke, as a consequence of blood pressure loweringTo enable scale-up of larger programs at the local, regional, and national levelsTo develop a better understanding of key barriers at local and national levels that affect hypertension control and how they can be overcomeTo understand how innovations for hypertension control can be introduced and scaled upTo improve hypertension control rates, particularly in vulnerable populations

## Methods

### Study Goals

The purpose of this study is to investigate the efficacy of an evidence-based system of SMS messages linked to accurately measured BP in the community. The individual BP measurements are taken by community health workers (CHWs). This innovation allows for transmission of accurate BP measurements from patients in isolated or underserviced populations to health care providers and, subsequently, improvement of patient knowledge about hypertension management. Participants in the Dream-Global study are randomized to receive either SMS messages that are both active and passive, compared with those receiving only passive messages. All messages are derived from the Hypertension Canada Clinical Practice Guidelines and are subsequently modified with community input to make them culturally sensitive and specific in both Canada and Tanzania [25]. The 12 active messages explain the importance of BP control, describe the rational for medical therapy, and, based on the BP reading, may instruct the participant to contact their health care provider for further BP follow-up. The 26 passive messages include health behaviors change advice for diet and exercise. Messages are sent twice weekly, on Monday and Thursday at 11 AM (to avoid holidays). The study is divided into five projects that involve the design, implementation, and then staging of the research program for the successful execution of a randomized controlled trial in both Canada and Tanzania.

*Project 1* is to develop a readiness to participate tool. The tool entails a multidimensional checklist intended to assess community readiness for implementation of a research program for hypertension awareness, treatment, and control. The tool developed was piloted in both Canadian Indigenous and Tanzanian communities participating in the Dream-Global study with evaluation and feedback for validation [24].

*Project 2* is a substudy to determine whether the sodium consumption of Indigenous people can be modified to help prevent hypertension. The goal was to plan and implement a food procurement policy for reducing sodium and fat intake from commercial food sources in an isolated Northern Indigenous community. This was approached by collating scientific evidence and existing policy recommendations, engaging community leaders and local food suppliers, and developing a policy approach for commercial food procurement practices. Evaluation includes process measures and examination of successes and barriers to implementation.

*Project 3* entails the development of a closed loop app to transmit BP results taken by the CHR in Canada and the CHW in Tanzania to the health care provider and to the participant in a manner consistent with personal health privacy rules in each country.

*Project 4* includes the development of a guidelines-based set of SMS messages in English that are culturally appropriate for Canadian First Nations communities and a set of SMS messages in Swahili that are culturally specific and appropriate for rural Tanzanian communities.

*Project 5* will evaluate the impact of the active and passive messages together, compared with that of passive messages alone on BP control over 1 year through a prospective, pragmatic, randomized controlled trial in both Canada and Tanzania.

### Blood Pressure Screening: Canada

In the Canadian Indigenous communities, the community nurse and CHR, a nonmedical health worker (analogous to CHWs in Tanzania), was trained in all aspects of the study, including BP measurement with the automated device, how to recruit, and how to consent participants. Consent was obtained from all participants, including the CHR, community nurse, and other members of the health care team and Band leadership who participated in surveys and interviews, as well as all participants for the BP measurement and lowering study.

Community leadership recommended that all interested individuals be allowed to participate as long as they are eligible. The study initially had focused on BP lowering, but to meet the community needs, a BP finding substudy was expanded to allow participants who were medically untreated but who screened below enrollment thresholds to participate. The screening BP was measured by trained Home and Community Care nurses or CHRs in community clinics using the BpTRU (BpTRU Medical Devices Ltd, Coquitlam, British Columbia, Canada), which takes six readings, omitting the first and averaging the final five. This BP reading, along with the participant’s baseline demographics, was recorded on a data collection form, which was deidentified and faxed back to the study center. Participants for the BP lowering study had to have uncontrolled hypertension while being on or off medications. Uncontrolled hypertension was defined as 140/90 mm Hg or above, or 130/80 mm Hg or above for participants with diabetes. In this way, only people on medications and who had BP controlled to target were not eligible. By limiting subjects who were ineligible for ongoing BP monitoring and SMS messages, the study met the needs of the community. It was recognized that some subjects who appeared to have controlled BP at screening might turn out to be uncontrolled and that some who appeared to be uncontrolled at screening might later turn out to be controlled.

Eligible participants were registered online. At registration, they were randomized electronically to receive active and passive SMS messages or passive only, and their names were then listed on the Dream-Global mobile app on the smartphone used by the Home and Community Care nurse or CHR in their community. BP was measured with the A&D UA-767PBT-C monitor (A&D Medical, San Jose, CA) to test that it was being transmitted properly; an SMS message to the participant’s registered mobile phone, with the BP reading, was the confirmation of transmission. The Home and Community Care nurse and CHR were trained to take three BP readings with this device. The study server was programmed in such a manner that it waits for up to three readings and then sends their mean to the participant’s own phone. Randomization through the study server ensured that participants and study personnel were blind to the allocation.

The baseline BP was defined as the mean of all readings from the A&D device in the first 2 months after randomization. If the average BP was uncontrolled during the first 2 months, the patient was identified as being in the BP lowering study; otherwise, they were followed up for BP screening. BP readings were stored on the central server, and deidentified data were transferred monthly to the data analysis center in Ottawa.

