### Blinding and Randomization

Participants were randomly allocated after enrollment using random number sequence with blocking of 2s and 4s for each community so that participants and study staff would not know which group participants had been enrolled. The randomization to receive active and passive or passive only text messages took place at the time of enrollment by the central server software. This information was available only to the database manager; participants, clinicians, and study staff had no knowledge of randomization.

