### Knowledge Translation and Engagement

Annual presentations will be made to each community on the study’s progress. At the end of the study, presentations are made to the community leadership, health care providers and participants, and community members through town-hall style meetings. Results will also be summarized in a poster for the communities. Annual presentations are made at the GACD study meeting, at which the other 14 study teams also present their updates.

Requirements of the Dream-Global app.Participants must be registered securely.Participants’ names will only show up on their community health resource’s or community health worker’s Dream-Global smartphone.Blood pressure readings on the A&D Medical monitor would transmit by Bluetooth to the smartphone.Blood pressure readings on the smartphone would be transmitted to the central server.A mean of the readings received by the central server would then be sent to the participant’s own phone (different from the community health worker’s smartphone).The central server will send the mean of the readings to the participant’s health care provider by fax in the form of a letter, based on the information provided at registration (Canada only).The server will be programmed to assess the blood pressure reading as normal or high and, if high for the participants receiving active messages, to advise them to see their health care provider for blood pressure management. In Canada, messages will include the phone number of their health care provider; in Tanzania, messages will include the location and weekdays on which the local blood pressure assessment clinic is running.

Abstracts will be presented at local, national, and international meetings as appropriate, and there will be publications in the peer-reviewed literature documenting the study progress and results. Furthermore, semiannual presentations will be made to Health Canada, specifically for the First Nations and Inuit Health Branch that funds the Home and Community Care health delivery in most First Nations communities. Semiannual progress reports are also submitted to the National Institute for Medical Research Tanzania. 

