### Blood Pressure Control Study and Primary and Secondary Outcomes

For the BP control study, the primary outcome is the difference between the two groups in BP change from baseline to study end (both systolic and diastolic). One year was chosen as a target for BP monitoring to allow for sufficient measurements and to reduce the Hawthorne effect, in which improved BP control from better adherence might occur for the period after study enrolment [34]. To reduce the effect of regression to the mean, the baseline BP was defined as the mean of the BP readings (each mean of three measures) taken with the A&D UA-767PBT-C in the first 2 months after enrolling in the study. The final BP measurement is the mean of the last 2 to 3 measurement days, usually in the last 2 months, to reduce variability from a single set of readings. The secondary outcome is the proportion of participants achieving BP control during the study period.

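### Baseline BP, and membership of the BP lowering cohort, are set by readings taken over the two months after randomization, so any early effect of the active messages is subtracted from the primary outcome and can alter who is compared

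*Protocol article*

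**What the plan says.** The baseline is defined twice, in agreement. Under Blood Pressure Screening: Canada: "The baseline BP was defined as the mean of all readings from the A&D device in the first 2 months after randomization". Under Blood Pressure Control Study and Primary and Secondary Outcomes, the readings are those "taken with the A&D UA-767PBT-C in the first 2 months after enrolling in the study". The latter section gives the reason: "To reduce the effect of regression to the mean, the baseline BP was defined as the mean of the BP readings". It makes the between-group difference in change from this baseline to study end, systolic and diastolic, the primary outcome.

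The Canadian screening section gives the two-month mean a second job. Participants whose average is uncontrolled over those months form the BP lowering study, and the rest are followed for screening.

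On timing, Blinding and Randomization says: "The randomization to receive active and passive or passive only text messages took place at the time of enrollment by the central server software". Study Goals sets two sends a week and describes 12 active and 26 passive messages. The app requirements under Knowledge Translation and Engagement add a step for one arm only. The server classifies each reading and is programmed, "if high for the participants receiving active messages, to advise them to see their health care provider for blood pressure management". No run-in or delayed message start is described.

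**The concern.** A baseline for a change score should not itself be open to influence by treatment. Here it is averaged over two months in which the arms appear to be treated differently already, and a high reading within the window can itself prompt advice in the active arm. Any between-arm difference that arises early is then subtracted from the primary contrast, which moves the estimate toward no difference.

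The stated reason does not require such a window. Regression to the mean is equal in expectation in randomized arms and cancels in their comparison. Averaging several days does reduce noise, but that is a gain in precision and does not answer an early arm-specific effect.

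The cohort rule raises a separate problem. An active-arm participant who responds quickly can average below the threshold and be moved to the screening group, while a comparable passive-arm participant stays. The two groups analysed are then not fully protected by randomization.

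**Working it through.** **1. The plan's own figure.** From Sample Size: diastolic difference 4.8 mm Hg, SDs of change 10.6 and 11, 176 per group, inflation factor 1.1729. A two-sided 0.05 level is assumed, as the article states none.

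- Effective number per group = 176 / 1.1729 = 150.1
- SE = √[(10.6² + 11²) / 150.1] = √(233.36 / 150.1) = 1.247 mm Hg
- Power = Φ(4.8 / 1.247 − 1.96) = Φ(1.89) = 97%

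This matches the stated 97%. That figure holds for the planned change score only if none of the 4.8 mm Hg is present in the baseline window.

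**2. Dilution.** Let δ be the true end-of-study difference and f the share of it present, on average, in months 0–2. The expected difference in change is δ − fδ = (1 − f)δ.

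**3. A range for f (assumption).** Suppose the effect builds linearly to its full size at month T (T of at least 2) and readings are spread evenly over months 0–2. The mean share in the window is then 1/T. For T = 12 the effect averages 11/12 of full size over months 10–12, so f = (1/12) / (11/12) = 9%.

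**4. Power = Φ[(1 − f) × 4.8 / SE − 1.96].** The last column uses 117 per group, half of the 234 enrolled according to Results: SE = √[233.36 / (117 / 1.1729)] = 1.530. It is an upper bound, because the 234 include screening participants.

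| Full effect reached at | f | Expected difference (mm Hg) | Power, 176 per group | Power, 117 per group |
|---|---|---|---|---|
| baseline free of effect | 0 | 4.80 | 97% | 88% |
| 12 months | 9% | 4.37 | 94% | 81% |
| 6 months | 17% | 3.98 | 89% | 74% |
| 4 months | 25% | 3.60 | 82% | 65% |
| 2 months | 50% | 2.40 | 49% | 35% |

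**5. Exposure in the window.** Two sends a week for two months is 2 × (52/12) × 2 ≈ 17 sends. If active messages were spread evenly (assumption), 12/38 × 17 ≈ 5 of these would be active. Only those, plus the advice after a high reading, can separate the arms.

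**6. Would adjustment for this baseline repair it?** No. The two-month mean as a covariate is still a post-randomization value that treatment may affect.

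**The case against.** The strongest reply is that the definition is deliberate, disclosed and consistent, and that the dilution runs toward no difference, so it would not by itself create a false positive. That is fair. So is the point that the loss may be small: if the effect builds over 6 to 12 months, power stays at about 89% to 94% at the planned size. Sample Size says extra power was built in for underrecruitment and a smaller difference. That margin can absorb part of the loss, though with 234 enrolled against a target of 360, some of it has gone already.

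Four stronger readings are tempting, and the article does not support them.

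- *Messages are known to run from the first day.* No start date is given. Overlap is inferred from randomization at enrollment, the twice-weekly schedule and the absence of a described run-in.
- *All 17 or so sends separate the arms.* Passive messages go to both arms, and each participant receives the BP reading whatever the allocation.
- *A null result could not be interpreted at all.* That does not follow across the plausible range of f, and f is zero if nothing arm-specific happens within two months.
- *The registration A&D reading is a pre-randomization baseline.* The Canadian screening section places it after electronic randomization. Only the BpTRU screening mean precedes randomization.

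**Conclusion.** The point holds. The primary change score starts from a post-randomization value and, as far as the article shows, one measured while messages are being sent. The bias is toward no difference and equals f times the true effect. The size cannot be computed from the article: at the planned sample size it ranges from nothing (97% power) through 82% at f = 25% to 49% at f = 50%. These figures rest on the planning effect and SDs, a two-sided 0.05 level, an assumed f and the inferred message start.

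Selecting the BP lowering cohort on the same mean is a second defect, and changing the outcome alone would not cure it. Its size cannot be computed from the article either. A reader might describe it as regression to the mean coming back, but that would be shared by the arms. The difficulty is selection on a variable that treatment may affect.

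**What to change.** 1. **Primary estimate.** Compare final A&D BP between arms, adjusted for the BpTRU screening mean (pre-randomization) and the first A&D reading at registration (after randomization, before any scheduled message; confirm from server time stamps). The BpTRU is a different device, so it suits use as a covariate better than as the value subtracted.
2. **Analysis population.** Define the BP lowering cohort by applying the protocol's existing thresholds to the screening BP or to that first A&D reading, not to the two-month mean.
3. **Sensitivity analysis.** Keep the two-month-mean change score and cohort, labelled as such.
4. **Message timing.** State when the first message was sent relative to randomization.

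No new data are needed, since both readings are part of the described procedures. The costs are these. A single-day value is noisier than a two-month mean; as a covariate this loses some precision but does not bias a randomized comparison. The registration reading may be fewer than three measurements, because the server waits for up to three. Canadian follow-up ended in December 2016, so this alters the primary analysis after data collection. It must be fixed before any unblinded analysis and disclosed as a change.
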